**Figure 2 F2:**
[figure not shown]
Sample Interactive Voice Response call design.

##### IVR return calls

The smoking cessation counseling is protocolized, uses a motivational interviewing style
[7] and focuses on providing behavioral techniques to help participants stay quit or re-start quit attempts and increasing adherence to smoking cessation medication. Behavioral counseling modules include managing withdrawal symptoms, craving, mood and stress, and accessing community resources for smoking cessation treatment. Medication management modules focus on medication instructions, managing side effects, and deciding when to stop medicine or change dose. Participants requesting refills are evaluated for side effects and all medication questions are answered.

### Measures

#### *Baseline*

Demographics are collected by chart review (gender, age, health insurance) and in the baseline survey (race/ethnicity, education, employment status, marital/partner status).

**Table 1 T1:** Helping HAND trial measures by assessment time point

**Measure**	**Baseline**	**Outcomes**		
		**1 Month**	**3 Month**	**6 Month**
Demographics	X			
Smoking History	X			
Nicotine dependence (FTND)	X			
Depression symptoms (CES-D)	X			
Alcohol use (AUDIT-C)	X			
Smoking status	X	X	X	X
Non-cigarette tobacco use	X	X	X	X
Biochemical validation^a^			X	X
Proxy validation^b^			X	X
Smoking during index hospital stay		X		
Readiness to quit smoking		X		
Confidence in ability to quit or stay quit		X		
Smoking cessation medication used		X	X	X
Smoking cessation counseling used		X	X	X
Healthcare utilization				
Hospital admission		X	X	X
Emergency room visit		X	X	X
Satisfaction with IVR^c^		X		

^a^Requested from self-reported nonsmokers only. Saliva cotinine requested by mail, unless participant is using nicotine replacement, in which case a visit for measurement of expired air CO is requested. ^b^Obtained from all participants, regardless of self-reported smoking status at outcome assessment. ^c^If the participant was not reached for the one-month follow-up, these questions were asked at the first follow-up for which the participant was reached. AUDIT-C, Alcohol Use Disorders Identification Test – Consumption; CES-d, Center for Epidemiological Studies 8-item Depression Scale; FTND, Fagerström Test for Nicotine Dependence; IVR, Interactive Voice Response.

Smoking history is collected during the hospital tobacco counseling visit and includes: cigarettes per day in the month prior to admission, use of non-cigarette tobacco products, age of smoking initiation, number of years smoking, quit history (ever tried to quit, length of longest quit), previous use of tobacco treatment (counseling, pharmacotherapy), living with a smoker, home smoking policy, in-hospital rating of cigarette craving, perceived importance of quitting, perceived confidence in ability to quit (ten point Likert scales), and intention to quit upon discharge from the hospital (‘I will stay quit’ or ‘I will try to quit’).

Nicotine dependence is measured using the Fagerström Test of Nicotine Dependence (FTND)
[41]. The FTND comprises six items with scores ranging from 0 to 10; higher scores indicate greater dependence.

##### Depression

Depressed mood is measured using the eight-item Center for Epidemiological Studies Depression Scale
[42] at baseline. Participants rate depressive symptoms over the past week on a four-point Likert scale. Scores range from 0–24, with higher scores indicating greater depression.

Alcohol use is assessed at baseline with the three-item Alcohol Use Disorders Identification Test – Consumption (AUDIT-C), which assesses quantity and frequency of alcohol use and frequency of binge-drinking episodes and generates a tailored risk rating
[43].

##### **Hospital admission characteristics**

Length of hospital stay, primary and secondary hospital discharge diagnoses, hospital service, and patient’s disposition after discharge (home or rehabilitation facility) will be obtained from hospital records.

#### *Follow-up (one, three and six months)*

##### Smoking status

The primary outcome is validated seven-day point prevalence abstinence from tobacco at six months after discharge. The principal secondary outcome measure is self-reported seven-day point prevalence abstinence at six months after discharge. Self-reported tobacco abstinence is defined as answering no to two questions: ‘In the past seven days have you smoked a cigarette, even a puff?’; ‘In the past seven days, have you used any tobacco product other than cigarettes such as cigars, pipes, snuff or chew?’ Patients who report tobacco abstinence are asked to provide biochemical and proxy validation (described above) for the primary outcome measure. Subjects who self-report smoking or whose cotinine or CO measures exceed the cut-offs (10 ng/ml for cotinine; 9 ppm for CO) are counted as smokers. Subjects with missing data (who are lost to follow-up or who self-report nonsmoking but do not provide a sufficient saliva sample, CO measurement, or proxy validation) are considered smokers for the primary analysis, but in secondary analyses, outcome will be imputed via statistical modeling.

Other secondary outcome measures of smoking status include: (1) self-reported seven-day point-prevalence tobacco abstinence at one and three months; (2) continuous abstinence from cigarettes and other tobacco (‘Since you left the hospital, have you smoked a cigarette, even a puff?’; ‘Since you left the hospital, have you used any tobacco product other than cigarettes such as cigars, pipes, snuff or chew?’), (3) prolonged abstinence, defined as not using tobacco at one, three and six month follow-up points; (4) duration of tobacco abstinence after discharge; (5) proportion of participants who make a 24-hour quit attempt after discharge (‘Since you left the hospital have you not smoked for 24 hours because you were trying to quit?’).

##### Stage of change/confidence

We assessed confidence (‘On a scale of one to ten, how confident are you that you will stay quit for the next year, with one being not at all confident and ten being very confident?’) among those who have quit or who have a specific plan to quit in the next 30 days. For those who are still smoking, we assess stage of change by asking if participants have ‘serious plans to quit in the next six months’ and ‘a specific plan to quit in the next 30 days’
[44].

##### Inpatient experience with tobacco abstinence and smoking cessation medication use

At the one-month follow-up (or the first follow-up completed), participants rate the difficulty that they had maintaining abstinence in the hospital (‘How hard was it not to smoke while you were in the hospital?’), using a four point Likert scale (not at all-very). Smoking while in the hospital is assessed (‘Did you smoke a cigarette, even a puff, during your stay in the hospital?’). Finally, we assess use of smoking cessation medications during hospitalization including use of the nicotine patch, nicotine gum, nicotine lozenge, nicotine inhaler, bupropion or varenicline.

##### Smoking cessation medication use/adherence

We assess post-discharge use of any of the FDA-approved smoking cessation medications including nicotine replacement (patch, gum, lozenge, inhaler, nasal spray), bupropion or varenicline. For those medications that are used we assess dose, frequency, duration of use and reason for termination. We also assess the source of these medicines (for example, provided by the study, obtained by prescription or purchased over the counter).

##### Post-discharge smoking cessation counseling use

Participants are asked whether they have spoken to a counselor or health care provider about their smoking since hospital discharge. Those who have spoken to a provider about their smoking are asked to whom they spoke (study counselor, state quitline, doctor, nurse, community counselor), how many times they received smoking cessation counseling, and the main topics discussed.

##### Post-discharge utilization of acute health care services

We assess emergency room visits and hospital readmissions during the six months after the discharge from the hospitalization at which enrollment occurred. Emergency room visits and hospitalizations are assessed two ways. First, an electronic medical record tracking system automatically notifies study staff whenever any participant is admitted to any emergency room or hospital in the Partners HealthCare System, the integrated health care delivery system to which MGH belongs. Second, participants are asked at each follow-up survey whether they have been to an emergency room or been hospitalized since their index hospital discharge. Questions are adapted from the 2008 National Health Interview Survey (‘Were you seen in an emergency room but not admitted to the hospital during the six months after you left MGH on (discharge date)?’; ‘Were you hospitalized anywhere overnight during the six months after you left MGH on (discharge date)? Do not include an overnight stay in the emergency room.’). These allow us to identify a hospitalization or emergency room visit made by a participant to a hospital outside Partners system. We request discharge summaries for admissions to hospitals outside Partners HealthCare System. Measures for health care utilization after discharge consist of: (1) number of hospital readmissions; (2) number of hospital days; (3) number of emergency room visits; (4) total number of hospitalizations and emergency room visits.

##### Satisfaction with IVR system

Participants in the Extended Care group who have answered at least one IVR call are asked three questions about satisfaction with the IVR (‘How helpful was it to get phone calls to check in about your smoking after you left the hospital?’ [very helpful-not at all helpful]; ‘If a friend or family member who smokes and wanted to stop were hospitalized, would you recommend that they be followed by an automated telephone support system to help them stop smoking?’ [strongly recommend-strongly not recommend]; and an open-ended question asking what was and was not helpful about the IVR).

#### *Quality assurance*

All referrals to the inpatient TTS and their disposition are recorded and monitored. Counselor screening forms and referrals are monitored to ensure that appropriate patients are being referred. Screening and recruitment reports are monitored weekly. Research staff meets with study counselors monthly to discuss any problems. Receipt of medication prior to discharge is tracked for each participant, and mailing medication used as the back-up strategy. The IVR web interface and IVR call completion rates are monitored weekly. All counseling sessions are recorded and 10% are reviewed for protocol adherence by a supervisor, a tobacco treatment counselor who is distinct from the one who delivered the treatment. Completion rates of follow-up assessments are reviewed weekly.

### Data analysis

#### *Sample size and power calculations*

We estimate that the primary outcome, verified seven-day tobacco abstinence rate at six-month follow-up, will be 20% among the Standard Care group and 35% among the Extended Care group. With a sample size of 165 per group, the study has 83% power to detect this difference with a 0.05 two-sided significance level. The estimate of the Standard Care cessation rate was extrapolated from three-month outcome data that was routinely collected from the MGH TTS. The rate ratio (35/20 = 1.75) was based on results of a recent meta-analysis
[8] but increased to reflect expected improvement due to project innovations.

#### *Comparison of smoking status outcomes*

The primary analysis will be done using the intention-to-treat perspective, regardless of whether patients in the Extended Care group took medications or participated in the IVR intervention. In the primary analysis, patients who are not reached for follow-up or who have not validated smoking cessation (either a saliva cotinine < 10 ng/ml, CO < 9 ppm or proxy verification) will be considered to be smoking. A secondary analysis will use multiple imputation techniques for missing biochemical verification values. Cross-sectional analyses will be conducted for outcomes assessed at one, three and six months after discharge.

Chi-square tests will be used to compare smoking cessation rates between the Extended Care group and the Standard Care group at each time point. Logistic regression analysis will be used to compare the two groups with age, sex, discharge diagnosis (cardiac versus other) and cigarettes smoked per day as the additional factors in the model. A longitudinal analysis using Generalized Estimating Equations (GEE) techniques will be used to assess the overall impact including data from all follow-up times while accounting for similarity in patient data across multiple assessment points. In a secondary analysis, we will use multiple imputation techniques for missing biochemical or proxy validation data. Self-reported seven-day point prevalence abstinence is the principal secondary endpoint.

Other smoking status outcomes compared between groups will be: (1) continuous abstinence; (2) prolonged abstinence (defined as quit at one, three and six months); (3) time to slip or relapse (first cigarette smoked after discharge); and (4) making a quit attempt (defined as intentionally not smoking for ≥ 24 hours) after discharge. Continuous and sustained abstinence and whether or not the participant made a quit attempt will be assessed using chi-square tests and logistic regression. Time to relapse will be assessed using survival analysis with Cox proportional hazards models. A secondary hypothesis is that participants in the Extended Care group will have higher rates of using smoking cessation pharmacotherapy and counseling than the Standard Care group. Use of pharmacotherapy and counseling will be assessed using chi-square tests.

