#### *Validation of tobacco abstinence*

Self-reported tobacco abstinence is validated in two ways at three and six month follow-ups: biochemically, and by asking a ‘proxy’ (a friend or family member of the participant) to confirm smoking status. We biochemically validate abstinence status for all participants reporting non-smoking, but we also contact proxies for all participants. First, participants who self-report being quit are asked to mail a saliva sample for assay of cotinine, a nicotine metabolite. Because nicotine replacement therapy (NRT) use produces detectable cotinine, the validation criterion for a patient reporting current NRT use is an expired-air carbon monoxide measurement of ≤9 ppm, obtained at a hospital or home visit
[39]. Participants are paid $50 for providing a sample for biochemical validation. We also validate smoking status by proxy report. At the baseline survey participants are asked to give the names of three people who would know whether they were smoking to serve as proxies. At three and six months, after the participant’s self-report is obtained, we call the participant’s proxy to obtain confirmation of the participant’s current smoking status. This is done for participants who report smoking as well as those reporting being abstinent. To ensure that proxies are good reporters of smoking status, we also ask when they last had contact with the participant.

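### The primary-endpoint rule is stated inconsistently: a failed cotinine or CO test makes a participant a smoker in the outcome section, but the analysis section, as worded, lets proxy verification validate the same participant

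*Protocol article*

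**What the plan says.** The primary outcome is fixed under Smoking status: "The primary outcome is validated seven-day point prevalence abstinence from tobacco at six months after discharge". Three sections of the protocol article bear on what *validated* means.

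- **Validation of tobacco abstinence** describes collection: "We biochemically validate abstinence status for all participants reporting non-smoking, but we also contact proxies for all participants". Saliva cotinine is the usual test. Participants currently using nicotine replacement have expired CO measured instead, with 9 ppm or less as the criterion.
- **Smoking status** (outcome definition) says "Patients who report tobacco abstinence are asked to provide biochemical and proxy validation (described above) for the primary outcome measure". For a failed test, participants "whose cotinine or CO measures exceed the cut-offs (10 ng/ml for cotinine; 9 ppm for CO) are counted as smokers". For missing validation, those who report not smoking but "do not provide a sufficient saliva sample, CO measurement, or proxy validation) are considered smokers for the primary analysis".
- **Comparison of smoking status outcomes** (analysis) counts as smokers those not reached and those whose cessation has not been validated. It lists the routes to validation in a parenthesis: "either a saliva cotinine < 10 ng/ml, CO < 9 ppm or proxy verification) will be considered to be smoking".

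**The concern.** The analysis section joins cotinine, CO and proxy with a plain *or*. It does not restrict the proxy route to participants who have no biochemical result. The outcome section says that a result above the cut-off makes the participant a smoker and gives the proxy no role in that case. The proxy is also not collected only as a back-up: it is sought for everyone, alongside the test. A failed test with a confirming proxy is therefore foreseeable, and an analyst following one section would code that participant differently from an analyst following the other.

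At stake is the definition of the primary endpoint. Participants know their allocation and name their own proxies, and validation is there to guard against misreporting. A rule that can be read as letting a nominated friend or relative outweigh a failed objective test weakens that protection. It also leaves the choice of reading open until the data are in view.

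**Working it through.** **1. The plan's own figure.** The sample size section states 83% power for 20% versus 35% validated abstinence, with 165 per arm and two-sided 0.05. With a continuity-corrected normal approximation, the mean rate is 0.275 and

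z = [0.15 − 1/165 − 1.96 × √(2 × 0.275 × 0.725/165)] / √[(0.20 × 0.80 + 0.35 × 0.65)/165] = (0.15 − 0.0061 − 0.0964)/0.0485 ≈ 0.98,

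which gives power of 83.7%. Fisher's exact test gives 84.2%; without the correction the figure is 86.6%. The stated 83% is consistent with the corrected or exact calculation. The power statement is not in error, and the point below does not depend on it.

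**2. The rules side by side**, for a participant who reports abstinence at six months:

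| Case | Validation section | Smoking status section | Analysis section, as written |
|---|---|---|---|
| Cotinine above 10 ng/ml or CO above 9 ppm; proxy confirms | Collects both; gives no order | Smoker | Validated abstinent |
| No usable sample; proxy confirms | Gives no order | Unclear: the missing-data list does not say whether one or all must be missing | Validated abstinent |
| CO exactly 9 ppm; no proxy | Meets criterion | Does not exceed cut-off | Not validated, so smoker |
| Cotinine exactly 10 ng/ml; no proxy | No cotinine cut-off given | Does not exceed cut-off | Not validated, so smoker |

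The first row is the substantive conflict. The last two are boundary mismatches: CO is ≤9 in one section, fails only above 9 in the second, and must be <9 in the third; cotinine must exceed 10 to fail in one section and be <10 to validate in another.

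**3. Size, under assumptions.** The document gives no rate of failed tests and no rate of proxy confirmation after a failed test. Let s be the self-reported abstinence rate, f the fraction of self-reported abstainers who fail the test, and q the fraction of failures confirmed by proxy. Suppose every self-reported abstainer gives a sample.

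- Failed test decides: rate = s(1 − f).
- Any one source suffices: rate = s(1 − f) + s·f·q.
- Change in the difference between arms: q(s₁f₁ − s₀f₀), with 1 for Extended Care and 0 for Standard Care.

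Assume s₁ = 0.40, s₀ = 0.28 and q from 0.3 to 0.7.

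*Equal failure, f = 0.20 in both arms.*
- Failed test decides: 0.40 × 0.80 = 32.0% and 0.28 × 0.80 = 22.4%, a difference of 9.6 points.
- Any source, q = 0.3: 34.4% and 24.1%, a difference of 10.3 points.
- Any source, q = 0.7: 37.6% and 26.3%, a difference of 11.3 points.
- Change: 0.024q, which is 0.7 to 1.7 points.

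*Unequal failure, to show what drives the result.*
- f = 0.30 in Extended Care and 0.15 in Standard Care: 28.0% − 23.8% = 4.2 points when the test decides; 6.5 to 9.7 points when any source suffices.
- The reverse, 0.15 and 0.30: 34.0% − 19.6% = 14.4 points when the test decides; adding q(0.06 − 0.084) = −0.024q gives 13.7 to 12.7 points.

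So both the size and the direction of the change depend on failure fractions that the document does not supply.

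**The case against.** The strongest reply is that the two sections fit together. The outcome section has a specific rule for a failed test, and directly after it a list for absent validation that closely resembles the parenthesis in the analysis section. The analysis section attaches its list to patients who were not reached, which is again a missing-data setting. On this view the parenthesis condenses the missing-validation rule, the failed-test rule still governs, and nothing in the text says that a proxy overrides a test.

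That reading is plausible and may be what was intended. It also disposes of one stronger inference a reader might draw, that the plan deliberately allows a proxy to overrule a positive test. The conflict comes from an unqualified *or*, not from a stated override. But the order of precedence is not written anywhere, and the request for biochemical *and* proxy validation points to yet another reading, in which both are required. The harmonising interpretation also leaves the mismatches at exactly 9 ppm and 10 ng/ml in place.

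A reader might also infer that a proxy with no contact in the past week could validate a seven-day claim. The document does not support that. It says "To ensure that proxies are good reporters of smoking status, we also ask when they last had contact with the participant", and how recent the contact must be is operating detail that a condensed article may leave to the full protocol.

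Finally, it is fair to object that the inputs for size are chosen, not taken from the document. Supposing a sample from every self-reported abstainer is generous, since saliva is mailed, CO needs a visit, and missing samples are anticipated; fewer samples mean fewer discordant cases.

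**Conclusion.** The point holds as an inconsistency in the wording of the primary-endpoint rule. For a self-reported abstainer with a failed test and a confirming proxy, the outcome section gives smoker and the analysis section, as written, gives validated abstinent. The design collects both sources, so the case can arise, and no stated order resolves it. The boundary values are a second, smaller inconsistency in the same rule.

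Its effect on the result cannot be derived from the document. With the assumed inputs above and equal test failure in both arms, the difference moves by about 1 to 2 points. The larger shift, from 4.2 to as much as 9.7 points, might tempt a reader to conclude that the endpoint is seriously biased towards Extended Care. It needs an assumed doubling of test failure in that arm, which nothing in the document supports; the opposite assumption shrinks the difference instead. The reason to act is that a primary outcome should give one value per participant under a rule settled before analysis.

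**What to change.** Amend the analysis section so that it follows the outcome section, and state the order once:

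1. Where a usable cotinine result exists (or a CO result for current nicotine-replacement users), that result decides.
2. Proxy confirmation counts only when no usable biochemical result exists.
3. Everyone else, including those not reached, is counted as smoking.

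The outcome section's request for both sources and its missing-validation list should be reworded to match. Use one set of inequalities for CO and cotinine in all three sections. The validation and outcome sections already agree on CO at exactly 9 ppm, so the least change is to bring the analysis section into line with them and to treat cotinine of exactly 10 ng/ml the same way.

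A sensitivity analysis using biochemical validation only, and a rule using the recorded date of the proxy's last contact, are optional additions and not corrections.

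The cost is a wording change. No new data item is needed: tests, proxy reports and last-contact dates are already specified. The trial status section puts the end of follow-up at November 2012, so the rule can be settled before analysis. Validated rates may come out slightly lower in both arms than if any single source sufficed.

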### Participants

#### Inclusion criteria

MGH inpatients are eligible for the study if they:

· Are an adult (≥18 years old).

· Are a current daily smoker (smoked ≥ 1 cigarette/day in the past month when smoking in their usual pattern).

· Plan to sustain or initiate a quit attempt after hospital discharge, assessed by asking the smoker to endorse one of four options (‘I will stay quit’, ‘I will try to quit’, ‘I don’t know if I’m going to quit’, ‘I do not plan to quit’). Only those smokers who endorse the first two responses are eligible for study enrollment.

· Have received smoking cessation counseling (for more than five minutes) and post-discharge smoking cessation medication recommendations from the MGH Tobacco Treatment Service staff.

· Are being discharged to home or, if discharged to a rehabilitation facility, have a mobile telephone on which they can receive the IVR calls.

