#### *Assignment to treatment group*

Participants are randomly assigned at the bedside to either Standard Care or Extended Care by research staff, in a 1:1 fashion in permuted blocks of eight randomization numbers. Randomization is stratified by two expected predictors of smoking cessation success, daily cigarette consumption in the month prior to admission (< 10 versus > = 10 cigarettes per day) and admitting service (cardiac versus other). Randomization is concealed by placing information about randomization condition into sealed envelopes. When a participant is randomized, the research staff member opens the next envelope corresponding to the participant’s randomization stratum, shares it with the participant, and initiates the assigned intervention. Research staff do not track the beginning and end of randomization blocks. Thus, neither the participant nor the research staff know participants’ randomization group before participants are enrolled.

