In designing the intervention, we considered whether to target all hospitalized smokers or only those who state an intention to quit smoking after discharge. We chose the latter approach, reasoning that less motivated smokers were unlikely to use the interventions, that the intervention would be most cost-effective for those intending to quit, and therefore a more targeted intervention would have the best chance of being adopted into clinical practice. This will likely increase cessation rates in both groups. While we believe that smokers planning to quit are the patients most likely to accept and benefit from our intervention, if it is successful, future studies could implement the intervention more broadly.

Our study design assesses the combined effect of an intervention package consisting of two components (IVR + medication provision) compared to standard care (counseling information and medication recommendation). This design does not permit us to determine the relative contribution of the individual intervention components (IVR/counseling or medication) to any effect that we might find. While a factorial design would allow us to distinguish the independent effects of counseling and medication, this would require a larger sample size. If the combined intervention proves effective, subsequent trials could examine the relative contributions of the counseling support and medication.

In summary, an evidence-based, cost-effective intervention model that is readily adoptable by US hospitals is needed in order to realize the potential impact of hospital-initiated smoking interventions and to meet new hospital quality measures under review. This trial is testing an intervention designed to meet this need. A cost-effective smoking intervention model for hospitalized smokers could, if widely adopted, help to reduce population smoking rates and thereby contribute to reducing tobacco-related mortality, morbidity, and health care costs.

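### The adjusted logistic model contains no motivation variable, although the baseline quit-intention answer is on file for every participant; adding it is a small, nearly free improvement

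*Protocol article*

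**What the plan says.** Under Inclusion criteria, patients choose one of four statements about quitting after discharge, and "Only those smokers who endorse the first two responses are eligible for study enrollment". Those two are *I will stay quit* and *I will try to quit*. Under Measures, Baseline, the smoking history taken at the hospital counseling visit, before randomisation, includes "intention to quit upon discharge from the hospital" with the same two categories.

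Under Comparison of smoking status outcomes, chi-square tests compare the arms at each time point. For the adjusted comparison the article states: "Logistic regression analysis will be used to compare the two groups with age, sex, discharge diagnosis (cardiac versus other) and cigarettes smoked per day". Intention is not among these covariates. Neither are perceived importance of quitting and confidence in quitting, which the baseline section also collects.

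On limiting entry to smokers who intend to quit, the Discussion says: "This will likely increase cessation rates in both groups".

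**The concern.** A baseline variable that predicts the outcome is useful in an adjusted model. It explains part of the outcome variation, which sharpens the treatment comparison, and it takes account of any difference in that variable between the arms. The trial limits entry by quit intention partly because it expects intention to go with cessation. A finer grade of the same variable is on file for everyone, but the published covariate list omits it.

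What is at stake is a little power in the adjusted analysis, and the standing of that analysis if the arms turn out to differ on the answer. If intention were added only after such a difference had been seen, the choice would look data-driven.

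**Working it through.** **Inputs from the protocol article.** Planned six-month abstinence is 20% in Standard Care and 35% in Extended Care. On size and power the article states: "With a sample size of 165 per group, the study has 83% power to detect this difference". The two-sided level is 0.05, and allocation is 1:1.

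**Inputs that must be assumed.** The article gives neither the share answering *I will stay quit* nor abstinence by answer. I take a share q of 30% to 70% and an odds ratio for abstinence between the two answers of 1.5 to 3, with overall abstinence held at 20% and 35%.

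**Step 1: the plan's own power.**
- Standard error under the null: √(2 × 0.275 × 0.725 / 165) = 0.0492.
- Standard error under the alternative: √((0.20 × 0.80 + 0.35 × 0.65) / 165) = 0.0485.
- Without continuity correction: Φ[(0.15 − 1.96 × 0.0492) / 0.0485] = 86.6%.
- With continuity correction, replacing 0.15 by 0.15 − 1/165 = 0.1439: 83.7%.

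The stated 83% is therefore reproduced with the continuity correction. It does not depend on any covariate.

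**Step 2: the effect of adjusting for the answer.** The variance of the adjusted risk difference is the mean within-answer binomial variance, summed over arms and divided by 165, plus q(1 − q)(RD₁ − RD₀)² / 330. RD₁ and RD₀ are the risk differences within each answer.

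Worked case, q = 0.5 and odds ratio 3. Abstinence by answer is 28.3% and 11.7% in Standard Care, and 47.1% and 22.9% in Extended Care.
- Within-answer variance: (0.1531 + 0.2129) / 165 = 0.002218.
- Second term: 0.25 × (0.188 − 0.112)² / 330 = 0.000004.
- Adjusted total 0.002222, against 0.3875 / 165 = 0.002348 unadjusted: a reduction of 5.4%.

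Over q = 30% to 70%:

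| Odds ratio between answers | Variance reduction | Power, continuity-corrected (83.7% unadjusted) | Power, uncorrected (86.6% unadjusted) |
|---|---|---|---|
| 1.5 | 0.6–0.8% | 83.9–84.0% | 86.8% |
| 2 | 1.7–2.3% | 84.3–84.5% | 87.1–87.3% |
| 3 | 3.7–5.4% | 85.1–85.7% | 87.8–88.4% |

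The gain is about 0.2 to 2 points.

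**Step 3: the comparison that matches the fix.** Step 2 compares no adjustment with adjustment for intention alone. The proposal adds a fifth covariate to a model that already has four. Simulating that logistic model with and without intention, with abstinence held at 20% and 35% and effects assumed for the other four covariates, gave a gain of about 0 to 2 points for odds ratios of 1.5 to 3 and about 3 points near 3.9. There was no material loss at an odds ratio of 1.

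**Step 4: chance imbalance.** If allocation ignores the answer, the between-arm difference in the share answering *I will stay quit* has SD √(2q(1 − q)/165). This is 5.0 points at q = 0.3 or 0.7 and 5.5 points at q = 0.5. A 1.96-SD imbalance is thus about 10 to 11 points. Multiplied by the gap in abstinence between the answers, it moves the estimated risk difference by about 0.8 points (odds ratio 1.5) to 2.2 points (odds ratio 3; 0.108 × 0.204 = 0.022). The unadjusted 95% half-width is 1.96 × 4.85 = 9.5 points and already includes this variation.

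**The case against.** The strongest objection is that nothing here is an error. The Discussion contrasts smokers who intend to quit with less motivated smokers; it does not contrast the two admitted answers, and no abstinence rates by answer are given. A short prespecified list of four covariates is defensible. The same case could be made for importance, confidence, nicotine dependence or depressive symptoms, all of which are collected. An analysis plan that is not shown may extend the list. All of this stands, and it is why the point is a refinement only.

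A reader might infer three stronger things, none of which the documents support.

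- *That the omission costs substantial power.* A gain of 7 points (79% to 86%) can be produced, but only with Standard Care abstinence of 35% and 5% by answer. That is an odds ratio of (0.35/0.65) / (0.05/0.95) = 10.2 between two adjacent favourable answers. It also requires fixing the conditional treatment effect at a log odds ratio of 0.85, so that Extended Care abstinence drifts below the planned 35%.
- *That chance imbalance biases the primary comparison.* Its expectation under randomisation is zero, and the chi-square standard error already covers it.
- *That randomisation should have been stratified on intention.* The two chosen strata are reasonable, and the Trial status section reports recruitment complete, so nothing could be changed.

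One part of the objection carries less weight. The covariate list is stated in the article, so the point concerns a published choice and not a gap left to another document. Intention also differs from the other candidates in being the variable on which the trial itself limits entry because it expects a link with cessation.

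**Conclusion.** The adjusted model omits a pre-randomisation motivation variable that is held for every participant. Adding it would raise the power of the adjusted comparison by about 0 to 2 points, assuming an odds ratio of 1.5 to 3 between the two answers, 30% to 70% answering *I will stay quit*, and overall abstinence of 20% and 35%. That the answers differ in prognosis at all is an assumption; if they do not, nothing material is lost. The sample size, the chi-square test and the validity of the design are unaffected. This is a nearly free improvement of low priority, not a mistake in the plan.

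**What to change.** In Comparison of smoking status outcomes, add baseline quit intention (*I will stay quit* versus *I will try to quit*, as recorded at the counseling visit) to the prespecified covariates of the logistic model for six-month abstinence. Use it likewise in the adjusted models for the other smoking outcomes. Fix this before analysis, so that the choice cannot depend on an observed imbalance.

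The cost is one sentence and one extra parameter, against about 91 expected abstainers (0.20 × 165 + 0.35 × 165 = 33 + 58). No new data are needed, and the chi-square comparison stays as planned.
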